#### Tertiary Outcomes

In order to conduct a cost-effectiveness analysis, we will estimate an ICER for two outcomes: number of times resources are provided to patients (health provider side) and smoking quit rates (patient side). The ICER will be calculated as the difference in discounted mean costs between intervention groups A and B divided by the difference in the outcome, using the following formula: ICER=(C_i_–C_c_)/(E_i_–E_c_), where C_i_ is the adjusted annual costs of group B, C_c_ is the adjusted annual costs of group A, E_i_ is the effect in group B, and E_c_ is the effect in group B. One-way deterministic sensitivity analyses will be performed to evaluate the robustness of our results.

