**Methods:**

The study design is a cluster randomized controlled trial of Family Health Teams participating in the Smoking Treatment for Ontario Patients program. Family Health Teams will be randomly allocated 1:1 to receive either generalized messages (related to depression and smoking) exclusively via email (group A) or be assigned a knowledge broker who provides personalized support through phone- and email-based check-ins (group B). The primary outcome, measured at the site level, is the proportion of eligible baseline visits that result in the provision of the mood management intervention to eligible patients.

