**Figure 1 figure1:**
[figure not shown]
Study workflow diagram.

The tertiary outcome will be a cost-effectiveness analysis (CEA), evaluating the delivery of each intervention from the health care system, and societal perspectives. The CEA will include the costs of developing, maintaining, and running each intervention in addition to costs associated with personnel, training, supplies, and services. The incremental cost-effectiveness ratio (ICER) will be the primary outcome of the CEA. An additional measure of interest will be the 95% confidence interval for the ICER, which will be estimated using nonparametric bootstrap resampling techniques [33-36]. This method is commonly used when undertaking economic evaluations alongside clinical trials [37,38].

Other outcomes measured in this study will include change in PHQ-9 score between the baseline and 6-month follow-up surveys, the proportion of eligible smokers who report using the materials, smoking cessation outcomes compared to patients without depression, and practitioner improvement in knowledge, attitudes, skills, and satisfaction in addressing depression in smokers.

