Some potential limitations should be acknowledged. As noted earlier, health care practitioners will not be blinded to the treatment allocation. During this study, a health care practitioner might work in two different clinics, one assigned to group A, and one to group B. In this case, there is the possibility of contamination of knowledge, as the health care practitioner might apply knowledge obtained from the KB advice received while working in a group B clinic to patients in their group A clinic. This possible contamination could decrease the trial effect and lead to a more conservative effect estimate. However, we anticipate that this will be a rare occurrence. In addition, there is a risk that detecting change in the abstinence rates may be underpowered when estimating the ICER for the economic evaluation.

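### The ICER definition misprints one effect term and words the provider-side effect as a count, and a bootstrap CI for the per-quit ratio would probably not be interpretable

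*Protocol article*

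**What the plan says.** Tertiary Outcomes gives ICER = (C_i − C_c)/(E_i − E_c). The costs are paired across arms: "C_i_ is the adjusted annual costs of group B, C_c_ is the adjusted annual costs of group A". The effects are not: "E_i_ is the effect in group B, and E_c_ is the effect in group B".

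Two effect measures are to be used: "number of times resources are provided to patients (health provider side) and smoking quit rates (patient side"). The Abstract (Methods) measures the first of these on another scale, as "the proportion of eligible baseline visits that result in the provision of the mood management intervention to eligible patients".

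The Outcomes section makes the ICER the main result of the economic evaluation and adds a "95% confidence interval for the ICER, which will be estimated using nonparametric bootstrap resampling techniques". Tertiary Outcomes adds deterministic sensitivity analyses that vary one input at a time. The Discussion concedes that "there is a risk that detecting change in the abstinence rates may be underpowered when estimating the ICER".

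**The concern.** There are three separate matters.

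1. **Label.** As printed, the denominator is group B minus group B.
2. **Scale.** A number of provisions depends on how many eligible patients each arm enrols as well as on what practitioners do. It is not the quantity that the primary analysis estimates. The section also speaks of mean costs in words and annual costs in the symbols, so it is unclear whether numerator and denominator share a per-patient basis.
3. **Uncertainty of the per-quit ratio.** When the effect difference is small against its standard error, bootstrap draws fall on both sides of zero. Draws just above and just below zero are nearly the same result, yet their ratios land at opposite extremes. A negative ratio can mean cheaper and better, or dearer and worse. Percentiles of such a mixture have no ordering that a decision maker can use. Deterministic sensitivity analyses do not address sampling error.

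At stake is whether the per-quit result can be read at all, and whether the per-provision result measures the knowledge translation strategy or enrolment.

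**Working it through.** **Inputs.** From Sample Size: provision 0.08 in control, risk difference 0.06 (so 0.14), ICC 0.032, cluster size CV 1.24, mean size 24, 1224 patients per group, alpha 0.05, power 0.80. From the Abstract: 33% quit rate at 6 months with depression. From the Introduction: quit gain of 12%-20% from mood management.

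**Reproducing the plan's own figure.** Two-sided, unpooled: (1.96 + 0.8416)² × (0.08×0.92 + 0.14×0.86)/0.06² = 423 per arm. Design effect for unequal clusters: 1 + ((1.24² + 1)×24 − 1)×0.032 = 2.917. The product is 1234, within 1% of the stated 1224, so the inputs are read as intended.

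**Count against proportion** (0.08 in A and 0.14 in B throughout):

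| Enrolled A | Enrolled B | Provisions A | Provisions B | Difference |
|---|---|---|---|---|
| 1224 | 1224 | 98 | 171 | 73 |
| 1346 | 1102 | 108 | 154 | 47 |
| 1102 | 1346 | 88 | 188 | 100 |
| 1400 | 800 | 112 | 112 | 0 |

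For a fixed cost difference, the second row raises the ratio by a factor of 73.44/46.60 = 1.58 and the third multiplies it by 73.44/100.28 = 0.73. The effect on practice is the same in every row. The last row is an extreme, shown only to make the mechanism clear.

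**Quit difference.** Assumptions: the broker affects quitting only through provision, the 12%-20% is in percentage points, and follow-up is complete. The article gives no ICC for quitting, so the design effect (DE) runs from 1.0 to 2.92. Difference d = 0.06 × gain. SE = √(DE × [0.33×0.67 + (0.33 + d)(0.67 − d)]/1224). The last column is the normal probability that the estimated difference is zero or negative. It is also roughly the share of bootstrap draws in a trial whose estimate falls at its expected value.

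| Gain | DE | d | SE | 95% half-width | z | P(≤ 0) |
|---|---|---|---|---|---|---|
| 0.12 | 1.00 | 0.0072 | 0.0191 | 0.037 | 0.38 | 0.35 |
| 0.12 | 2.92 | 0.0072 | 0.0326 | 0.064 | 0.22 | 0.41 |
| 0.20 | 1.00 | 0.0120 | 0.0191 | 0.037 | 0.63 | 0.26 |
| 0.20 | 2.92 | 0.0120 | 0.0326 | 0.064 | 0.37 | 0.36 |

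- If all 128 FHTs enrol 24 patients on average (1536 per arm), P(≤ 0) is 0.24 to 0.40.
- If the gain is relative to 33%, d is 0.0024 to 0.0040 and P(≤ 0) is 0.45 to 0.47 at DE 2.92.
- Missing 6-month surveys, which the article expects, would widen the SE.
- For d to equal its 95% half-width, the provision difference would have to be between 0.0374/0.20 = 19 points and 0.0638/0.12 = 53 points, against the 6 planned.

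**What the limits would look like.** With a cost difference fixed at an illustrative 100 units and DE 2.92, the simulated 2.5 and 97.5 percentiles of the ratio are about −48,000 and +49,000 (true value 100/0.0072 = 13,900), or −46,000 and +45,000 (true value 100/0.012 = 8,300).

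**Provision as a proportion.** SE = √(2.917 × (0.0736 + 0.1204)/1224) = 0.0215, z = 0.06/0.0215 = 2.8, P(≤ 0) about 0.003. That denominator is stable.

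**The case against.** The strongest reply is that this is one misprint plus preference.

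- **The label.** A reader might infer that the ICER cannot be computed. The text does not support that: the same passage describes the ratio in words as a comparison of groups A and B, Trial Design identifies group A as control, and the control cost is correctly assigned to group A. A correction is still needed.
- **The count.** It may be shorthand, since the outcome is defined elsewhere as a proportion and as yes or no per patient. Randomisation is 1:1 and stratified on expected clinic size, which limits imbalance. One could compute an SD of 24 × 1.24 × √64 × √2 = 337 patients for the difference in arm enrolment, but that ignores the stratification and is not a figure for this design. What stands is that the wording names a count and should not.
- **The quit calculation.** The article states no expected between-arm quit difference and no ICC for quitting, so the result is derived under assumptions. This stands as a caveat, but the conclusion holds across the range tested.
- **Disclosure.** The Discussion already warns of low power. That is fair, but the warning changes neither the measure nor the interval.
- **The resampling unit.** A reader might infer that patients will be resampled and the intervals will be too narrow. Nothing says so, and Statistical Analysis commits to methods that respect clustering.
- **Objective 3.** A reader might infer that it fails. The Abstract frames that objective around implementation, that is, provision, where the ratio on the proportion scale is stable.

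**Conclusion.** The point holds as a correction to a tertiary analysis.

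The control effect is mislabelled, with the intent evident from its context. The provider-side effect, if followed as worded, would vary with enrolment: 47 to 100 extra provisions for opposite 10% shifts around a value of 73. For quits, the expected difference of 0.7 to 1.2 points is only 0.22 to 0.63 of its standard error, and about 26% to 41% of draws would have a zero or negative denominator. A 95% percentile interval for that ratio could not be interpreted. An exact (Fieller) set would be unbounded whenever the effect difference is not significant at the 5% level.

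The quit result rests on the broker acting only through provision, on the percentage-point reading and on the design-effect range. A direct effect of the broker on quitting would weaken it; the relative reading or missing follow-up would strengthen it. The primary analysis, the secondary analysis, the randomisation and the sample size are untouched.

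**What to change.** 1. Define E_c as the effect in group A.
2. State the provider-side effect as the primary-outcome proportion and the patient-side effect as the proportion abstinent, both per eligible patient, with costs on the same per-patient basis.
3. Resample FHTs in the bootstrap, in line with the commitment to cluster methods. From the same replicates report incremental net benefit, λ(E_i − E_c) − (C_i − C_c), over a stated range of willingness to pay λ, with the cost-effectiveness plane and acceptability curve. Use this as the uncertainty summary, at least for quits, in place of the ICER confidence interval. Net benefit involves no division, so its interval is well defined when the effect difference is near zero.
4. Fix this choice in advance. A rule that drops the interval only when the observed effect interval includes zero would depend on the data and is not recommended.

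The cost is a text correction and revised wording for the economic analysis, with no new data. The downside is that the headline for quits becomes a curve and not a single ratio with limits, and a willingness-to-pay range has to be chosen and justified.

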### Ethical Approval and Trial Status

The study was reviewed by the Research Ethics Board at the Centre for Addiction and Mental Health (approval number: 065-2016). The trail is registered with ClinicalTrials.gov (ID: NCT03130998). At the time of manuscript submission, the readiness survey was administered, but recruitment was not completed.

## Results

Recruitment for the primary outcome of this study will be completed in 2018/2019. Results will be reported in 2019/2020.

## Discussion

It is well known that the process of integrating research evidence into practice is slow and complex [42]. Even though there have been many strategies evaluated to improve how health care professionals care for their patients, there is still no clear answer as to which is the most effective, and cost-effective, strategy to use [16,17]. Two strategies that are commonly used to promote practice change include (1) tailored and targeted messages that connect relevant research evidence to practice users [43]; and (2) KBs who work one-on-one with decision makers to facilitate evidence-informed decision-making [16].

This clinical trial will address the knowledge gap in the implementation approach associated with the use of email-based prompts versus a KB in mood management interventions for smokers with depression in primary care settings. With at least one life saved from a tobacco-related death for every two smokers who quit [44], the potential patient-level impact will extend well beyond the study duration. Assuming both approaches are equally effective at achieving a modest probability (10%) of practice change and knowing there should be a 12%-20% improvement in the likelihood of quitting smoking due to use of a mood management intervention, we would expect 19 to 32 patients with depression to quit smoking. An additional benefit to patients will be a potential improvement in their depression scores as a result of the specialized care and resources provided by clinicians as part of this study.

In addition, the Web-based portal used by STOP overcomes the issue of compatibility across various electronic medical records in FHTs. Adding a depression intervention to this system could lead to a system-wide implementation of integrated depression care pathways at a relatively low cost, potentially reaching 2.25 million Ontarians registered at these FHTs. Moreover, a technology-based KB model will help reduce travel costs and expand the reach of KBs in the future.

Finally, rapid and efficient implementation in other settings participating in the STOP program, such as Community Health Centres, addiction agencies, Public Health Units, and Nurse Practitioner–Led Clinics, is possible at a relatively low cost. We will also have high quality data on these populations for planning and monitoring the effects of interventions in primary care settings.

Some potential limitations should be acknowledged. As noted earlier, health care practitioners will not be blinded to the treatment allocation. During this study, a health care practitioner might work in two different clinics, one assigned to group A, and one to group B. In this case, there is the possibility of contamination of knowledge, as the health care practitioner might apply knowledge obtained from the KB advice received while working in a group B clinic to patients in their group A clinic. This possible contamination could decrease the trial effect and lead to a more conservative effect estimate. However, we anticipate that this will be a rare occurrence. In addition, there is a risk that detecting change in the abstinence rates may be underpowered when estimating the ICER for the economic evaluation.

## Abbreviations

CEA: cost-effectiveness analysis
FHT: Family Health Team
GEE: generalized estimating equation
ICC: intracluster correlation
ICER: incremental cost-effectiveness ratio
ICP: integrated care pathway
KB: knowledge broker
KT: knowledge translation
OR: odds ratio
PHQ-9: Patient Health Questionnaire
STOP: Smoking Treatment for Ontario Patients
